## 5.5 Criteria for study suspension

During the study period, subjects will be monitored for the following ADRs that serve as criteria for study suspension. In the event of ADRs that are the criteria for study suspension, additional enrollment and treatment will be stopped at this time, and the DSMB will meet to decide study continuation.

- 1) Part A study: Grade  $\geq 3$  ADRs occurring within 7 days after the 1st dose in the first 5 subjects
- 2) Part A and Part B studies:
  - ① Grade  $\geq 3$  ADRs occurring within 3 days (Day 0 ~ Day 2) from the respective dosing day and lasting for  $> 1$  day despite active intervention for resolution in  $\geq 15\%$  of all

subjects planned to be enrolled to each study group (Part A:  $\geq 8/50$  subjects, Part B:  $\geq 35/230$  subjects)

- ② SADRs or Grade  $\geq 4$  ADRs occurring within 28 days after the respective dose of the IP

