##### 3.1.1 Part A

Part A consists of two dose levels (low dose, high dose) of EuCorVac-19. Each dose group consists of 15 subjects in test group and 10 subjects in placebo group.

The first 5 subjects will be randomized and enrolled to the low dose group (Sentinel group: 3 subjects in Test group, 2 subjects in Placebo group); once the safety of the IP is confirmed in these subjects over 7 days after the 1st dose of the IP, the study will proceed to enroll the rest of 20 subjects to the low dose group. The rest of 20 subjects will be randomized to 12 subjects in Test group and 8 subjects in Placebo group. Also, the first 5 subjects will be randomized and enrolled

to the high dose group (Sentinel group: 3 subjects in Test group, 2 subjects in Placebo group); If no Grade  $\geq 3$  adverse drug reactions (ADRs) are reported within 7 days (Day 0 ~ Day 6) after the 1st dose of the IP, the rest of 20 subjects to the high dose group will be enrolled. The 20 subjects in the high dose group will be randomized to 12 subjects in Test group and 8 subjects in Placebo group.

If Grade  $\geq 3$  ADRs are reported within 7 days after the 1st dose of the IP in any of the first 5 subjects (Sentinel group) in each dose groups, the Data and Safety Monitoring Board (DSMB) will review the safety of the IP and determine whether to continue the study. If applicable, subject enrollment will be stopped and additional dosing in the existing subjects suspended until the decision is made on study continuation.

Once the safety results up to 28 days after the 2nd dose are collected from all subjects in Part A, the DSMB will review the safety data from all subjects enrolled in the high and low dose groups in Part A. The DSMB will assess if the event of ADRs in all subjects meet the criteria for study suspension and figure out the relationship between ADR and IP, based on which proceeding to Part B will be decided.

An interim analysis will be conducted using the immunogenicity data collected up to 21 days after the 2nd dose and the safety data collected up to 28 days after the 2nd dose in all subjects enrolled in Part A. Additional interim analysis will be performed using the safety and immunogenicity data collected up to 26 weeks after the 2nd dose in all subjects enrolled in Part A.

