### **3.3.2 Part B**

Subjects will be assigned to each treatment group in a ratio of 10:10:3 (low dose group: high dose group: placebo comparator group) and stratified by age (19 to 50 years of age versus 51 to 75 years of age). The randomization manager will randomly choose a block size amongst the multiples of the number of treatment groups and generate randomization tables using the SAS

(version 9.4 or above) program.

Individuals who provide written informed consent to participation in Part B will be given a screening number in the order of written informed consent. The screening number will consist of [2-digit number representing the study institution]-SB-[3-digit serial number]. Afterwards, those who meet the inclusion/exclusion criteria will be randomized by central randomization plans in which subjects are stratified by age. In the order of enrollment as determined by the investigator, the subjects will be given a unique randomization number consisting of [2-digit number representing the study institution]-RB[1-digit stratification code\*]-[3-digit serial number].

(\*stratification code '1': 19 to 50 years of age, '2': 51 to 75 years of age)

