## **5. Subject selection and withdrawal criteria**

### **5.1 Inclusion criteria**

To be eligible for enrollment, individuals must meet all of the criteria described below.

- 1) Individuals who voluntarily decide to participate in this study and provide written informed consent:
  - Healthy male and female adult at the age of 19 to 50 years (Part A)
  - Healthy male and female adult at the age of 19 to 75 years (Part B)
- 2) Individuals who, after receiving detailed explanations about the study, voluntarily decide to participate in this study and provide written informed consent
- 3) Individuals who are available for all visit procedures including telephone visits during the study period

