##### 7.1.1.2 Part B

To obtain 195 subjects who have at least one dose of the IP after randomization and are available for immune response analysis, at least 230 eligible volunteers based on the inclusion/exclusion criteria will be enrolled considering the drop-out rate of 15%. At least 15% (35 subjects) of overall subjects will be recruited from those between 51 and 75 years of age.

|                                                           | Low dose group | High dose group | Placebo comparator group |
|-----------------------------------------------------------|----------------|-----------------|--------------------------|
| Number of immune response analyses                        | 85 subjects    | 85 subjects     | 25 subjects              |
| Total number of subjects considering drop-out rate of 15% | 100 subjects   | 100 subjects    | 30 subjects              |

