### **7.3.7 Planned interim analysis and safety monitoring**

Upon completion of data collection from all subjects in Part A up to Day 28 after the 2nd dose of the IP (end of main study, Visit 9), DB lock will be carried out for a data analysis based on which interim study results will be presented.

Also, upon completion of data collection from all subjects in Part A up to Week 26 after the 2nd dose of the IP (Visit 10), DB lock will be carried out on those collected data and the interim study results will be presented.

The data from all subjects in Part B up to Day 28 (end of main study, Visit 9) will be collected and DB lock on these data will be carried out for a data analysis. The interim study results will be presented.

Subsequently, once all subjects in Part A and Part B complete the study (end of follow-up, Visit 11), DB lock will be carried out, and the final results will be presented.

For the purpose of safety monitoring, the principal investigator will serve as the protocol safety manager based on the level of risk involved in this study. During the study period, the principal investigator will monitor according to the protocol the safety of subjects participating in the study at the applicable institution.

Whenever an SAE and/or an ADR occurs, the principal investigator will collect and review the data of the relevant subject as well as relevant safety information. In the event of an AE, unexpected issue, or a protocol non-compliance, the principal investigator will report to the sponsor (including the CRO), the IRB, and if necessary, the Ministry of Food and Drug Safety (MFDS) according to the protocol, the IRB-specific regulations, Good Clinical Practice (GCP), and other applicable regulations. In addition, if efficacy and safety information that might have a significant impact on the continuation of the study according to Section 9.11. 'Early termination or suspension of the study' in the protocol becomes known, the principal investigator will report to the sponsor in a timely manner, and in turn, the sponsor will discuss and decide on study continuation according to the sponsor's SOP.

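### The only count-based suspension rule in Part B is pooled over ages, so it is a weak trigger for persistent Grade 3 reactions in adults aged 51 to 75, who have no earlier exposure; a by-stratum count would be a cheap improvement

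*Protocol*

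**What the plan says.** Section 5.5 of the protocol lists three suspension criteria.

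- Criterion 1) applies only to the first five subjects in Part A.
- Criterion 2)① counts subjects with a Grade 3 or higher ADR that starts on Day 0 to Day 2 and lasts more than a day despite active treatment. The limit is 15% of all "subjects planned to be enrolled to each study group", worked out as 8 of 50 in Part A and 35 of 230 in Part B.
- Criterion 2)② has no count. It covers serious or Grade 4 and higher "ADRs occurring within 28 days after the respective dose of the IP".

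On age, section 5.1 restricts the first part: "Healthy male and female adult at the age of 19 to 50 years (Part A"). The DSMB reviews Part A safety data, "based on which proceeding to Part B will be decided" (section 3.1.1). For Part B, section 7.1.1.2 says: "At least 15% (35 subjects) of overall subjects will be recruited from those between 51 and 75 years of age". Section 3.3.2 allocates 10:10:3 to low dose, high dose and placebo, "stratified by age (19 to 50 years of age versus 51 to 75 years of age").

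On oversight during Part B, section 7.3.7 schedules the first analysis after Day 28: "The data from all subjects in Part B up to Day 28 (end of main study, Visit 9) will be collected". It also provides: "Whenever an SAE and/or an ADR occurs, the principal investigator will collect and review the data of the relevant subject". Section 7.3.8 has the DSMB meet in Part B when a suspension criterion is met and, if necessary, for adverse events of special interest. It refers to a DSMB charter for details.

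**The concern.** Nobody over 50 receives the vaccine before Part B, and Part B has neither a sentinel group nor a staggered start for them. The sponsor treats persistent Grade 3 ADRs in 15% of planned subjects as reason to stop and call the DSMB. Because the count is pooled, that standard bears little on the older stratum, which makes up only about 15% of Part B at its minimum size. Many older vaccinees could have a non-serious but persistent Grade 3 reaction without ① being met. A compulsory DSMB review would then depend on one of the reactions becoming Grade 4 or serious. Safety and tolerability at ages 19 to 75 is Part B's secondary objective (section 2.2).

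**Working it through.** **1. The plan's own figures.** 0.15 × 50 = 7.5, rounded up to 8. 0.15 × 230 = 34.5, rounded up to 35. The minimum of older subjects is the same product, 35. All three reproduce.

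**2. Older subjects who receive vaccine.** 35 × 20/23 = 30.4 (30 used below), with 35 × 3/23 = 4.6 on placebo. Younger: 230 − 35 = 195, and 195 × 20/23 = 169.6 (170 used). If all 30 older vaccinees qualified, the count would be 30/230 = 13.0%, below 15%. If placebo reactions judged related under the blind also counted, every one of the 35 older subjects would have to be affected.

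**3. Where impossibility ends.** N × 20/23 ≥ 35 requires N ≥ 40.25. At 41 older subjects (35.7 vaccinated), older events alone need a rate of 35/35.7 = 98%; at 69 (60 vaccinated), 35/60 = 58%.

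**4. Chance that ① is met.** P(X + Y ≥ 35), with X ~ Bin(30, p) for older and Y ~ Bin(170, q) for younger vaccinees. The protocol gives no event rates, so p and q are assumed; no placebo events.

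| Younger rate q | p = 30% | p = 45% | p = 50% |
|---|---|---|---|
| 0% | 0 | 0 | 0 |
| 5% | 0.00002 | 0.001 | 0.004 |
| 10% | 0.038 | 0.20 | 0.30 |

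**5. Chance that ① or ② is met.** Let a share s of reactors at any age reach Grade 4 or a serious ADR. The chance is 1 minus the sum, over i + j < 35, of C(30,i)(p(1−s))^i(1−p)^(30−i) × C(170,j)(q(1−s))^j(1−q)^(170−j). ② events outside the reactors are ignored.

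| p, q | s = 1% | s = 5% | s = 10% |
|---|---|---|---|
| 30%, 0% | 0.09 | 0.36 | 0.60 |
| 30%, 5% | 0.16 | 0.58 | 0.83 |
| 50%, 5% | 0.21 | 0.69 | 0.91 |

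**6. The same 15% within the older stratum.** 0.15 × 35 = 5.25, rounded up to 6.

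| True older rate | 30% | 20% | 15% | 10% | 5% |
|---|---|---|---|---|---|
| P(Bin(30, p) ≥ 6) | 0.92 | 0.57 | 0.29 | 0.07 | 0.003 |

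These need complete data on all 30 vaccinees. With 15 evaluable, the chance is 0.28 at 30% and 0.06 at 20%.

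**7. What the stratum count adds.** The chance that it is met while no reactor of any age has met ② is Σ(i ≥ 6) C(30,i)(p(1−s))^i(1−p)^(30−i) × (1 − qs)^170. The sum is 0.391 / 0.263 at p = 20% and 0.574 / 0.353 at p = 30%, for s = 5% / 10%. The last factor is 0.653 / 0.427 at q = 5% and 0.427 / 0.181 at q = 10%.

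| | p = 20%, s = 5% / 10% | p = 30%, s = 5% / 10% |
|---|---|---|
| q = 5% | 0.26 / 0.11 | 0.38 / 0.15 |
| q = 10% | 0.17 / 0.05 | 0.25 / 0.06 |

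**8. Why the count must scale.** With 80 older subjects, 80 × 20/23 is about 70 vaccinees. A fixed 6 would fire with probability P(Bin(70, 0.10) ≥ 6) = 0.71 at a true 10% rate. The scaled count is 0.15 × 80 = 12.

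**The case against.** Section 5.5 states a rule for stopping the whole study. Nothing in the protocol promises stopping by subgroup, so nothing is contradicted or miscalculated, and any pooled rule is insensitive to a subgroup of about 15%. That stands, and it makes this an improvement rather than an error.

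Other protection is substantial:

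- Criterion ② acts on a single event at any age. Grade 4 includes an emergency room visit for several solicited reactions, such as pain, headache and myalgia (section 8.3.1).
- Subjects must telephone in Grade 3 or higher events (section 8.2). A call on Days 2 to 5 and a Day 7 visit precede the second dose, which can be withheld (section 5.3).
- The principal investigator reviews each ADR and reports information that might affect continuation to the sponsor, who decides (section 7.3.7) and may terminate (section 9.11.1).

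A reader might therefore infer that the older group is either fully covered or unmonitored. Neither follows. Required safety action exists; what is missing is an obligation to bring a stratum-wide pattern of non-serious Grade 3 reactions to the DSMB. The charter might contain one, but it is not shown.

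Two limits on the remedy also stand. Younger vaccinees may trigger ② first, which reduces what a stratum count adds. A count reached after most older subjects are dosed protects few, and the protocol gives no accrual speed.

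**Conclusion.** The point holds as a low-cost safety refinement, offered for the sponsor's consideration. At 35 older subjects, about 30 of them vaccinated, non-serious persistent Grade 3 ADRs confined to the stratum cannot meet ①. It would be tempting to say that older rates of two to three times 15% would almost never meet it. That is fair only if younger vaccinees react at about 5% or less; at 10% the chance is 20% for an older rate of 45%. Nor can one say that the rule is unreachable in general, because 35 is a minimum and younger events count too.

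The size of the gap turns on how often reactions escalate. Criterion ② closes much of it if about 10% of reactors reach Grade 4 or become serious, and little of it at 1%. All event rates and escalation shares are assumptions, and the conclusion concerns only what the protocol itself fixes.

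**What to change.** Add to sections 5.5 2)① and 7.3.8: in Part B the same criterion is also counted among subjects aged 51 to 75. The threshold is 15% of the number planned for that stratum over all arms, rounded up: 6 at 35, 7 at 46, 12 at 80. The sponsor should state that planned number, since the protocol gives only a minimum. Reaching the threshold pauses enrolment and dosing in that stratum and convenes the existing DSMB, which decides on continuation. A stratum-only pause differs from the general stop in section 5.5 and needs its own sentence there.

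The cost is protocol and charter wording plus a count by stratum. The age stratum is already coded in the randomization number (section 3.3.2), no new committee is needed, and an all-arm count needs no unblinding. The downside is a possible extra DSMB meeting (about 7% at a true 10% rate with 35 older subjects) and, if dosing is paused, some second doses outside the +5-day window of Visit 5.

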## **5.6 Study compliance and handling of protocol deviations**

To prevent protocol deviations, the principal investigator and the sub-investigator should be fully familiar with, and thoroughly comply with the protocol. To comply with IP dosing and testing schedules in this study, the sub-investigator will take adequate measures to ensure that subjects return for all outpatient visits by, for instance, issuing a written notice of the next visit time or performing telephone monitoring. Should protocol deviations occur, they will be notified to the responsible clinical research associate (CRA) or the sponsor and reported within the timeline as appropriate according to the Institutional Review Board (IRB)-specific regulations.

## 6. Investigational product

### 6.1 Overview of investigational product

#### 6.1.1 Test drug

##### 6.1.1.1 Low dose group

- Code name: EuCorVac-19 (COVID-19 recombinant protein vaccine)
- Appearance and formulation: clear, yellow-green liquid in a clear, colorless vial for injection
- Storage condition: to be refrigerated at 2~8°C
- Shelf-life: up to 12 months from the date of manufacture (to be extended based on the stability test results if available)
- Drug substance and its content:

per 1 vial(0.5 mL)

| Purpose                  | Drug substance                           | Specification | Content | Unit |
|--------------------------|------------------------------------------|---------------|---------|------|
| Active ingredient |                                          |               |         |      |
| Main raw material        | RBD Antigen                              | In-house      | 10      | µg   |
| Excipients        |                                          |               |         |      |
| Solubilizing agent       | EcML                                     | In-house      | 10      | µg   |
| Solubilizing agent       | CoPoP                                    | In-house      | 20      | µg   |
| Solubilizing agent       | DOPC                                     | In-house      | 0.4     | mg   |
| Solubilizing agent       | Cholesterol                              | EP            | 0.1     | mg   |
| Buffer                   | Disodium hydrogen phosphate heptahydrate | USP           | 0.36    | mg   |
| Buffer                   | Potassium dihydrogen phosphate           | EP            | 0.11    | mg   |
| Isotonic agent           | Sodium chloride                          | EP            | 4.50    | mg   |
| Solvent                  | Water for injection                      | EP            | q.s.    |      |

##### 6.1.1.2 High dose group

- Code name: EuCorVac-19(COVID-19 recombinant protein vaccine)
- Appearance and formulation: clear, yellow-green liquid in a clear, colorless vial for injection
- Storage condition: to be refrigerated at 2~8°C
- Shelf-life: up to 12 months from the date of manufacture (to be extended based on the stability test results if available)
- Drug substance and its content:

In one vial

| Purpose                  | Drug substance                           | Specification | Content | Unit |
|--------------------------|------------------------------------------|---------------|---------|------|
| Active ingredient |                                          |               |         |      |
| Main raw material        | RBD Antigen                              | In-house      | 20      | µg   |
| Excipients        |                                          |               |         |      |
| Solubilizing agent       | EcML                                     | In-house      | 20      | µg   |
| Solubilizing agent       | CoPoP                                    | In-house      | 40      | µg   |
| Solubilizing agent       | DOPC                                     | In-house      | 0.8     | mg   |
| Solubilizing agent       | Cholesterol                              | EP            | 0.2     | mg   |
| Buffer                   | Disodium hydrogen phosphate heptahydrate | USP           | 0.36    | mg   |
| Buffer                   | Potassium dihydrogen phosphate           | EP            | 0.11    | mg   |
| Isotonic agent           | Sodium chloride                          | EP            | 4.50    | mg   |
| Solvent                  | Water for injection                      | EP            | q.s.    |      |

### 6.1.2 Placebo (for Part B only)

- Product name: Dai Han Isotonic Sodium Chloride Inj. (sodium chloride)
- Appearance and formulation: clear, colorless, slightly salty solution in a clear, colorless a plastic) container of water for injection
- Storage condition: store in a sealed container at ambient temperature (1~30°C)
- Shelf-life: 36 months from manufacturing date
- Composition(per 20mL):Sodium chloride(active ingredient) 180 mg, water for injection(excipient)

## 6.2 Dosage, method, and duration of treatment

Subjects will receive 0.5mL of either the low or the high dose of the IP(EuCorVac-19) or placebo(Dai Han isotonic sodium chloride inj.) on the deltoid muscle for two times. The 2nd dose will be given 21 days after the 1st dose.

The IP will be prepared according to the IP manual for administration to the subject. Prior to dosing, the appearance of the IP will be examined; the IP with any abnormalities will not be administered. If the filled volume of the IP and placebo exceeds the recommended dosage, the remaining substances will be discarded in accordance with the regulation of the institution or the guidance provided by the sponsor.

## 6.3 Manufacturing, packaging, and labeling of the investigational product

The IP will be manufactured or purchased by the sponsor and supplied to the pharmacist at the study institution.

The label of the IP will be prepared according to “Regulations for the Manufacturing and Quality Control of Medicinal Products, Attachment 11. Manufacturing of Investigational Products” and bear the following information.

1. For clinical investigation only (e.g., “for clinical trials”)
2. Name or identification of the IP
3. Batch no. or code no. to identify the content and packaging
4. Sponsor (IND holder)’s name, address, and telephone number
5. Expiry date (shelf-life)
6. Storage conditions
7. Reference code to identify the study
8. If necessary, subject identification no., treatment no., visit no., investigator’s name, method of application

If the primary package is too small to bear all of the above-mentioned information, minimum information (for clinical trials/name of the IP or identification no./batch no. or code

no./sponsor/reference code/study drug no./shelf-life) will be labeled on the primary package, and all information will be labeled from the secondary package according to Appendix 11 of Regulations for the Manufacturing and Quality Control of Medicinal Products.

#### **6.4 Management of the investigational product**

- The test drug will be stored at 2~8°C, and the comparator (placebo) will be stored at ambient temperature (1~30°C). The study drug cannot be used without the instruction (prescription) of the principal investigator and the sub-investigator.
- The sponsor should supply the IP directly to the pharmacist upon agreement with the principal investigator and should maintain the receipt.
- The pharmacist should ensure that the IP is not used for any purpose other than the clinical trial by properly storing and managing the IP. The pharmacist is responsible for receiving the IP, maintaining the inventory, dispensing the IP to each subject, and returning the IP. The pharmacist should document relevant records and inform the principal investigator on a regular basis.
- During the course of the study, the sponsor should check the quantity and storage conditions of the IP and take necessary actions for appropriate study conduct.
- In the event of suspension or termination of the study or any issues with the IP or expiration of the IP, the sponsor will retrieve and destroy any unused IPs. In this case, the pharmacist should return all unused IPs to the sponsor and maintain the return receipt.
- During the study, the container of the IP dispensed to the subject and used will be immediately destroyed on site upon use according to site-specific regulations and guidelines provided by the sponsor, and relevant document should be maintained.

